#### Primary outcome measure

The primary outcome measure of this study is the Hopkins Symptom Checklist (HSCL-25). This assesses anxiety and depression symptom levels at 3-month follow-up assessment [31]. It has 25 items, namely two sub-scales for depression (13 items) and anxiety symptoms (10 items) and two items related to somatic symptoms. These items are scored on a 4-point Likert scale.

#### Secondary outcome measures

The secondary outcome measures are (1) the PTSD Checklist for DSM-5 (PCL-5) to assess the severity of post-traumatic stress reactions, (2) Psychological Outcomes Profiles (PSYCHLOPS) to assess self-identified problems, (3) the Client Service Receipt Inventory (CSRI) to assess health service utilization and productivity impacts, and (4) WHODAS, which is also part of the screening and which assesses functional disability [32, 33]. In addition, perceived access to health services will be measured (see Fig. 2). The PCL-5 has 20 items scored on a 0–4 scale, adding up to a total severity score of 80, and higher scores indicate higher levels of symptomatology. PSYCHLOPS consists of four questions on three domains: problems (two questions), function (one question) and wellbeing (one question). Problem and function questions are asked in the form of free texts, and the responses are scored on an ordinal 6-point scale, producing a maximum score of 20. The CSRI includes questions about resource use for health and social care services, informal care, and productivity as a result of functionality in people with mental disorders. The CSRI has been adapted for Syrians in Turkey to match Turkish health-care services that are available to Syrians. Relevant unit costs will be attached to service utilisation to estimate changes in use of health services and health-care costs, while Turkish minimum wage rates will be used to conservatively estimate changes in costs associated with both informal family care and lost productivity by the patient from work.

#### Other measures

A self-constructed questionnaire will be used to assess lifetime trauma exposure. This questionnaire includes items from the Harvard Trauma Questionnaire (HTQ) and the Post-traumatic Diagnostic Scale (PDS) and asks questions on specific traumatic experiences of Syrian refugees. It has 28 items scored as 0 (no) or 1 (yes), and the total score ranges from 0 to 28 [34, 35].

The Post-Migration Living Difficulties Checklist (PMLDC) will be used to assess post-migration stressors. The PMLDC has 17 items scored on a 5-point scale, ranging from 0 to 4 (0 = not a problem and 4 = very serious problem) (range 0–68). Items scored at least 2 (a moderately serious problem) are considered positive responses [36, 37].

If the validated Arabic version of the included measures is available, they will be selected and tested through cognitive interviews with Arabic-speaking adult Syrians. If the validated Arabic version of the measures is not available, these measures will be translated and back-translated in accordance with the WHO guidelines [38].

All randomly assigned participants, including those who discontinue, will be invited to all outcome assessments. In case participants do not attend a scheduled outcome assessment, they will be called a maximum of five times (on different days) to schedule a new appointment.

#### Process evaluation

We will explore the feasibility, challenges and success of the intervention through semi-structured interviews with facilitators, PM+ participants, policy makers and health professionals. From each category, five participants will be included. Interviews will take between 30 and 60 min and will start after ICs are obtained from the participants. Moreover, PM+ dose (i.e., number of sessions completed), treatment fidelity and quality will be assessed. Participant adherence to the intervention will be monitored by recording their attendance to sessions. Attendance to fewer than three sessions will be counted as dropout. Facilitators will be allowed to deliver PM+ sessions with participants after training and a competency assessment. Facilitators receive weekly supervision to ensure that intervention content is adhered to. Moreover, facilitators will be asked to complete a structured checklist on the Group PM+ components immediately after completion of each session. Trained staff members will be present during 10% of the PM+ sessions and will score treatment fidelity by using a checklist of the required PM+ elements [39].

We will promote participant retention by sending text messages to participants to remind them of their appointments. We will also regularly update phone numbers and other contact information of participants. Moreover, we offer weekend and evening hours for group sessions and outcome assessments and provide a child-friendly place for children. This may facilitate treatment access and may have a positive impact on participant retention. Participants who come to group sessions and outcome assessments will be reimbursed for travel*.*

### Data management

All data will be handled confidentially by the data monitoring committee, which consists of two researchers from Istanbul Sehir University (ISU). Quantitative data will be collected either through pen-and-paper format or through tablets. The quantitative data and the identifying key (a list connecting names to numbers) will be kept in a separate and secure locked location at the Trauma Research Lab at ISU. The data will be entered into a data-analytic computer program without the identifying key.

Qualitative interviews will be saved separately from the participants’ identifiers and will be transcribed and safely stored at the Trauma Research Lab at ISU. There will be no audio data since the Immigration Authority of Turkey does not give permission to make audio recordings in research studies with Syrian refugees (see ‘Ethics approval and consent to participate’ section).

## Statistical methods

Descriptive analyses will be carried out in Statistical Package for the Social Sciences (SPSS) and Hierarchical Linear Modelling (HLM) analyses in Stata version 11.2. Across all analyses, two-tailed tests will be reported with a *P* value of less than 0.05. To estimate the effectiveness and cost-effectiveness of Group PM+, the following data analysis methods will be conducted. First, to examine whether there are differences between conditions, *t* tests (continuous variables) or chi-squared test (categorical variables) will be conducted at baseline to compare the two intervention arms (i.e., Group PM+/E-TAU vs. E-TUA) for normally distributed data; Mann–Whitney tests will be conducted for continuous non-normally distributed data.

Intention-to-treat (ITT) analyses, including all randomly assigned participants (*N* = 380) and treatment completers’ (per protocol) analyses, will be conducted. The primary outcomes of the trial will be the ITT analyses. A linear mixed model will be used for the primary endpoint analysis to estimate the intervention effect, which will have intervention as fixed effects, baseline measurement of primary endpoint as covariate, and participants as random effects.

The mean difference between the two treatment arms at each visit/time together with its 95% confidence interval will be derived from the mixed model. A covariate-adjusted mixed model for the primary endpoint will be performed by adding pre-specified covariates at baseline (gender, age, education, traumatic experiences, post-migration difficulties, etc.) into the above model. Missing data will be treated as missing at random. No imputations of missing values will be made, as multilevel models can deal with missing data [40]. Qualitative data from the process evaluation will be analysed thematically in accordance with the framework approach [41]. Interview transcripts will be coded by using Nvivo version 11 [42].

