#### Sample size and power calculations

The Vrije University (VU) University Medical Centre Department of Epidemiology and Biostatistics carried out the power calculations for this study. Considering previous studies with PM+ in Peshawar, Pakistan, and Nairobi, Kenya, we aim for a conservatively estimated small to medium Cohen’s d effect size of 0.4 in the PM+ group at the 3-month follow-up [13, 15]. Power calculations suggest a minimum sample size of 133 participants per group (power = 0.90, a = 0.05, two-sided). Considering an expected 30% attrition at the 3-month follow-up, we aim to include a total number of 380 participants (190 in the Group PM+/E-CAU group and 190 in the E-CAU group).

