#### Randomization

After baseline assessment, participants will be randomly assigned on a 1:1 basis to either Group PM+/E-CAU (*n* = 190) or E-CAU (*n* = 190) (T0). Randomization using computerized software will be carried out by an independent researcher who is not involved in the intervention delivery, clinical supervision, assessments or other aspects of the study.

There is a chance that participants of the study will be recruited from the same household, creating a risk for contamination (if family members were to be allocated to receive different treatments, namely either Group PM+ or E-CAU). To limit the likelihood of contamination, participants from the same household will be assigned to the same intervention arm.

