### Group PM+

PM+ is a brief, trans-diagnostic psychological intervention based on cognitive behavioural therapy techniques and developed by the WHO [12, 27]. It consists of five sessions delivered in five consecutive weeks and aims to reduce symptoms of depression, anxiety, PTSD and related conditions. Groups are separated by gender, and gender-matched facilitators will lead groups consisting of six to eight participants (T1). Sessions include evidence-based strategies of stress management, problem-solving, behavioural activation and strengthening social support. PM+ is designed to be delivered by non-specialist helpers who receive an 8-day training in PM+. These Arabic-speaking non-specialist helpers, who are called facilitators, are supervised by psychologists and psychiatrists who have participated in the PM+ training-of-trainers program. Supervision consists of weekly, face-to-face group supervision and individual supervision when needed.

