### Enhanced usual care

Syrians in Turkey have free access to mental health services in public hospitals and migrant health centres [28]. However, owing to numerous barriers such as lack of knowledge of available mental health services or (self)stigma, the use of mental health services is low among Syrian refugees [29, 30]. Usual care will be enhanced by providing study participants with a leaflet on publicly available mental health services in the area where they live. Implementing Group PM+ or E-CAU will not require alteration to usual care pathways (including use of any medication) and these will continue for both trial arms.

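### The secondary treatment-completer (per-protocol) analysis can select on attendance only in the PM+ arm, so it may be confounded; a complier average causal effect should replace it as the estimate in those who received PM+

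*Protocol article*

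**What the plan says.** The Statistical methods section plans an ITT analysis of all 380 participants and a second analysis of treatment completers, and ranks them: "per protocol) analyses, will be conducted. The primary outcomes of the trial will be the ITT analyses". It does not define a completer or say which E-CAU participants form the comparison group.

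The only attendance rule is under Process evaluation: "Attendance to fewer than three sessions will be counted as dropout". It refers to PM+ sessions, and the Group PM+ section says of the intervention: "It consists of five sessions delivered in five consecutive weeks". The control arm has no counterpart. Under Enhanced usual care: "Usual care will be enhanced by providing study participants with a leaflet on publicly available mental health services in the area where they live".

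Two other statements bear on the remedy. Follow-up does not stop when treatment stops: "All randomly assigned participants, including those who discontinue, will be invited to all outcome assessments". Baseline adjustment is planned, but is described for the primary endpoint and not tied to the completer set: "A covariate-adjusted mixed model for the primary endpoint will be performed by adding pre-specified covariates at baseline".

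**The concern.** Randomisation makes the two whole arms comparable. It does not make PM+ attenders comparable with the whole E-CAU arm, which also contains people who would not have attended had they been offered sessions. If attenders differ in prognosis from non-attenders, the completer comparison mixes that difference with the effect of PM+.

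Such a difference is plausible. Under Process evaluation, the plan offers sessions outside working hours, somewhere for children to be, and repayment of travel costs, to ease access. It therefore expects work, childcare and money to influence attendance, and these may also relate to later distress. Motivation is a further candidate that the listed baseline covariates do not measure.

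What is at stake is the secondary estimate, which readers are likely to take as the effect in people who actually received PM+. The trial can estimate that quantity from data it already plans to collect, without comparing a selected group with an unselected one.

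**Working it through.** **The plan's own figure.** From Sample size and power calculations: d = 0.4, power 0.90, two-sided alpha 0.05. The normal formula gives n = 2(1.960 + 1.282)²/0.4² = 2 × 10.51/0.16 = 131.3, so 132 per arm. The t-test version gives 132.3, so 133, as stated. With 30% attrition, 133/0.70 = 190 per arm and 380 in total. The sample size reproduces and is not in question. The 30% is loss to assessment and says nothing about session attendance.

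**Inputs the article does not give (assumed).**
- Share of the PM+ arm that does not complete: 25% to 40%.
- Difference in 3-month prognosis between completers and non-completers, after baseline adjustment: 0.3 SD, non-completers worse.

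**Bias with no treatment effect.** Completer mean minus whole-arm mean = non-completer share × prognosis gap.
- 25%: 0.25 × 0.3 = 0.075 SD; 0.075/0.4 = 19% of the planned effect.
- 40%: 0.40 × 0.3 = 0.12 SD; 0.12/0.4 = 30% of the planned effect.

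If non-completers had the better prognosis by the same amount, both figures would change sign and count against PM+.

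**Cross-check with a second model.** Let completers be the top share c of a normal attendance propensity that has correlation rho with the baseline-adjusted outcome. Bias = rho × φ(z_c)/c, where φ is the standard normal density and z_c the normal quantile of c. The rejection rate assumes a true effect of zero, 133 analysed in E-CAU and c × 133 in PM+.

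| c | rho | Bias (SD) | Share of d = 0.4 | Rejection rate at nominal 5% |
|---|---|---|---|---|
| 0.9 | 0.1 | 0.02 | 5% | 5.3% |
| 0.9 | 0.3 | 0.06 | 15% | 7.5% |
| 0.7 | 0.1 | 0.05 | 12% | 6.6% |
| 0.7 | 0.2 | 0.10 | 25% | 11.5% |
| 0.7 | 0.3 | 0.15 | 37% | 20.1% |
| 0.5 | 0.1 | 0.08 | 20% | 8.3% |
| 0.5 | 0.3 | 0.24 | 60% | 36.9% |

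With rho = 0 there is no bias and the rate is 5.0%. In this model the prognosis gap is rho × φ(z_c)/(c(1 − c)). A gap of 0.3 SD therefore corresponds to rho = 0.3 × 0.1875/0.318 = 0.18 at c = 0.75, and 0.3 × 0.24/0.386 = 0.19 at c = 0.60. The two calculations agree.

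**The alternative.** E-CAU is offered no sessions, so non-adherence is one-sided and the complier average causal effect is ITT effect/c.
- If the ITT effect is zero, the complier effect is zero whatever the prognosis gap.
- Its interval is wider by about 1/c: 1/0.75 = 1.33 to 1/0.60 = 1.67. Without covariates, the ITT half-width at 133 per arm is 1.96 × √(2/133) = 0.24 SD. It becomes 0.24/0.75 = 0.32 SD and 0.24/0.60 = 0.40 SD, treating c as known.
- If those attending fewer than three sessions gain δ on average, ITT = cτ + (1 − c)δ, where τ is the effect in completers. The estimate is then τ + δ(1 − c)/c, an excess of 0.33δ at c = 0.75 and 0.67δ at c = 0.60.

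**The case against.** The strongest reply is that the plan already puts this analysis in its place. ITT is primary, those who discontinue are still invited to assessments, and the sample size does not depend on the completer set. A reader might infer that the trial's main conclusion is compromised. The document does not support that.

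Second, a reader might take it as stated that attenders of at least three sessions will be compared with the whole E-CAU arm. It is not stated. The three-session rule sits under Process evaluation and labels dropout, and the Statistical methods section does not refer to it. An analysis plan not shown here could define the set further or add adjustment. This stands as a caution about the exact form. It does not remove the point: sessions exist in one arm only, so any attendance-based set selects in that arm alone, and baseline adjustment helps only as far as the measured covariates explain attendance.

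Third, the inputs are assumed, and an unadjusted gap of 0.3 SD would overstate the bias. That is right, and it is why the gap is taken as residual.

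Fourth, the complier estimate is a rescaled ITT effect. It adds little independent evidence of efficacy and brings assumptions of its own. One or two sessions of a five-session programme may have some effect, and loss to assessment may go with non-attendance. These objections stand as stated costs. They do not make the completer comparison the better estimate.

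**Conclusion.** The point holds for the secondary completer analysis only. That analysis appears to compare selected PM+ attenders with unselected E-CAU participants and is confounded if attendance relates to prognosis beyond the baseline covariates. The primary ITT result is untouched.

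Under 25% to 40% non-completion and a residual gap of 0.3 SD, the bias is about 0.075 to 0.12 SD, or 19% to 30% of d = 0.4. Its sign is unknown. A reader might infer that the bias rivals the planned effect, or that it must favour PM+. Neither follows. The 60% figure needs the most extreme pair examined (50% completion, correlation 0.3), the article supports neither value, and the bias reverses if people with worse prognosis attend more. If attendance is unrelated to residual prognosis, there is no bias.

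This is an inexpensive improvement worth making, not a threat to the trial's conclusion.

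**What to change.** Keep ITT primary. Make a complier average causal effect at the 3-month assessment the estimate of effect in those who received PM+, with randomised arm as the instrument for attending at least three sessions and the same baseline covariate as the primary model. If the completer comparison is kept, define the set and label it exploratory and non-causal.

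A version with number of sessions as the dose can be added as a sensitivity analysis. With one binary instrument it is just-identified: it replaces the threshold assumption with a linear dose-response and does not test whether fewer than three sessions has no effect.

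The change needs analysis-plan wording and minor programming. It needs no new data, because attendance is already recorded and discontinuers are already invited to assessments. The price is a wider interval, the assumption that attending fewer than three sessions has no effect, and reliance on the missing-at-random assumption already made, here for the 30% expected attrition.

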**Methods:**

A randomized controlled trial (RCT) will be conducted with 380 Syrian refugees in Turkey. After providing informed consent, participants with high levels of psychological distress (scoring above 15 on the Kessler-10 Psychological Distress Scale (K10)) and functional impairment (scoring above 16 on the WHO Disability Assessment Schedule 2.0, or WHODAS 2.0) will be randomly assigned to Group PM+/enhanced care as usual (Group PM+/E-CAU) (*n* = 190) or E-CAU (*n* = 190). Outcome assessments will take place 1 week after the fifth session (post-assessment), 3 months after the fifth session and 12 months after baseline assessment. The primary outcome is psychological distress as measured by the Hopkins Symptom Checklist (HSCL-25). Secondary outcomes include functional impairment, post-traumatic stress symptoms, self-identified problems, and health system and productivity costs. A process evaluation will be conducted to explore the feasibility, challenges and success of the intervention with 25 participants, including participants, facilitators, policy makers and mental health professionals.

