### Outcome measures

All instruments will be administered by trained research staff blind to the allocation status of the participants at post-assessment (1 week after the fifth PM+ session) (T1), 3 months after the baseline (T2) and 12 months after baseline (T3).

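### The primary mixed model, as listed, has no visit or arm-by-visit term, so it cannot give the by-visit differences promised from it or the 3-month difference that is the primary outcome

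*Protocol article*

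**What the plan says.** All places are in the protocol article.

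- **Model.** Statistical methods gives the terms of the linear mixed model for the primary endpoint: "which will have intervention as fixed effects, baseline measurement of primary endpoint as covariate, and participants as random effects".
- **Output.** The following paragraph begins: "The mean difference between the two treatment arms at each visit/time together with its 95% confidence interval will be derived from the mixed model".
- **Adjusted model.** The covariate-adjusted version is obtained by "adding pre-specified covariates at baseline (gender, age, education, traumatic experiences, post-migration difficulties, etc.) into the above model". It adds baseline variables only, so visit does not enter there either.
- **Primary outcome.** Of the HSCL-25, the section Primary outcome measure says: "This assesses anxiety and depression symptom levels at 3-month follow-up assessment".
- **Sample size.** Sample size and power calculations assumes a "small to medium Cohen’s d effect size of 0.4 in the PM+ group at the 3-month follow-up" and arrives at a "minimum sample size of 133 participants per group (power = 0.90, a = 0.05, two-sided". This is raised to 190 per arm for 30% attrition at 3 months.
- **Visits.** There are three follow-up assessments: post-assessment (T1), 3 months (T2) and 12 months (T3).

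**The concern.** A participant random effect, together with differences at each visit, implies that the T1, T2 and T3 records are analysed jointly. If arm and baseline are then the only fixed effects, the fitted arm difference is one number, the same at every visit. The model cannot deliver the output that the next sentence assigns to it.

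The section calls the target simply the intervention effect and does not say which contrast carries the primary test. One analyst could report the pooled coefficient, following the listed terms. Another could report the 3-month contrast, following the outcome and sample-size sections. Both could claim to follow the protocol. The choice between them should not be open once data are seen, because the two answers can differ when the effect of a five-week intervention changes over 12 months.

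**Working it through.** **1. The plan's own figure.** A two-sample t-test with d = 0.4, two-sided alpha 0.05 and power 0.90 needs 132.3, so 133 per arm. Then 133 / (1 − 0.30) = 190 per arm, 380 in total. The sample size reproduces, and it is computed for the 3-month difference.

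**2. Inputs for the model check.** From the protocol: 190 per arm, three visits, 70% retained at 3 months. Assumed, because the article does not give them: outcome SD 1; retention 80% at T1 and 60% at T3, equal in both arms, with monotone dropout; correlation 0.5 between visits and 0.5 between each visit and baseline; a random intercept. Given baseline, the residual variance is 1 − 0.5² = 0.75, the residual covariance is 0.5 − 0.25 = 0.25, and the residual correlation is r = 0.25 / 0.75 = 1/3.

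**3. What the listed model estimates.** With arm as the only non-baseline fixed effect, the coefficient is a weighted mean of the three true effects. A participant with m visits contributes 1 / (1 + (m − 1)r) to each visit attended, which is 1, 0.75 or 0.6 for m = 1, 2 or 3. The shares of participants with 1, 2 and 3 visits are 0.1, 0.1 and 0.6.

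- T3: 0.6 × 0.6 = 0.360
- T2: 0.360 + 0.1 × 0.75 = 0.435
- T1: 0.435 + 0.1 × 1 = 0.535
- Sum: 1.330, so the weights are 0.402, 0.327 and 0.271 for T1, T2 and T3

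The standard error is √(2 × 0.75 / (190 × 1.330)) = 0.077.

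**4. Results for assumed true effects (SD units).**

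| T1 / T2 / T3 | True 3-month effect | Listed model gives | 95% CI covers the 3-month effect |
|---|---|---|---|
| 0.4 / 0.4 / 0.4 | 0.40 | 0.40 | 95% |
| 0.5 / 0.4 / 0.3 | 0.40 | 0.41 | 94.7% |
| 0.5 / 0.4 / 0.2 | 0.40 | 0.39 | 94.6% |
| 0.4 / 0.4 / 0.3 | 0.40 | 0.37 | 93.6% |
| 0.4 / 0.4 / 0 | 0.40 | 0.29 | 71% |
| 0.5 / 0 / 0 | 0 | 0.20 | 26% |

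In the last row the probability of declaring benefit is Φ(0.201 / 0.077 − 1.96) = Φ(0.65), about 74%, although the 3-month effect is zero. A 3-month contrast would do so 2.5% of the time.

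**5. Sensitivity.** Without baseline adjustment (variance 1, r = 0.5) the contributions sum to 1.133, the weights are 0.412, 0.324 and 0.265, and the standard error is √(2 / (190 × 1.133)) = 0.096. The 74% becomes Φ(0.206 / 0.096 − 1.96), about 57%, and the 71% becomes about 80%. Over r = 0.3 to 0.7 the ranges are 53 to 63% and 76 to 83%.

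**6. With visit and arm-by-visit terms.** The T2 contrast equals the true 3-month effect in every row. Its standard error by generalised least squares is about 0.105. As a hand check, the 133 observed at 3 months alone give √(2 × 0.75 / 133) = 0.106. Without baseline adjustment the standard error is 0.121, and power at 0.4 is Φ(0.4 / 0.121 − 1.96), about 0.91, so the planned 0.90 is kept.

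**The case against.** The best defence is that the list of terms is abbreviated. The sentence that follows it asks for visit-specific differences, which need visit and arm-by-visit terms. The authors therefore probably meant to include them, and a condensed article may leave a full model statement to the full protocol or analysis plan. This stands as a reading of intent. A reader might infer from the listed terms that the trial will test a pooled effect and so answer the wrong question. The documents do not support that, since no sentence says a pooled effect will be reported or tested.

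The defence does not remove the contradiction. The article chose to state the model's terms, and those terms cannot produce the output it then promises. Intent also does not tell the reader which of the by-visit differences is the primary test.

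The large errors in the table come from assumed and fairly extreme trajectories, with no effect left at 12 months. Under mild decay the listed model would be almost right. That stands, and it is why the size must be given as a range.

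A reader might also fault the covariance structure, ask for a baseline-by-visit term, or expect the time trend to leak into the arm effect. The documents do not establish any of these as errors. Participants as random effects does not fix a random intercept with independent residuals. The baseline-by-visit term is a preference. The leak needs attrition that differs by arm, which the protocol does not predict.

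**Conclusion.** The point holds as an internal contradiction in the stated primary analysis. The listed terms yield one effect pooled over T1 to T3. The text promises a difference at each visit, and the outcome and sample-size sections rest on the 3-month difference, which is never named as the primary test.

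The numerical consequence is conditional on the model being fitted exactly as listed, and on the assumed retention and correlations. It runs from nothing for a constant effect, through about 0.01 SD for mild decay, to 0.11 SD too low for 0.4/0.4/0 and 0.20 SD too high for 0.5/0/0. The false declaration of benefit in that last case is about 74%, or about 57% without baseline adjustment. The sample size is not in question.

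**What to change.** In Statistical methods, add visit (categorical: T1, T2, T3) and arm-by-visit to the fixed effects of the stated model, keeping baseline HSCL-25 and the participant random effect. State that the primary test is the arm contrast at the 3-month visit from the intention-to-treat model, and that the T1 and T3 contrasts are secondary. The covariate-adjusted model then inherits the same terms.

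The visit that carries the primary contrast also needs one definition. The abstract has assessments "3 months after the fifth session and 12 months after baseline assessment", whereas Outcome measures has them "3 months after the baseline (T2) and 12 months after baseline (T3". The two must be reconciled.

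The cost is wording, with no change to recruitment or conduct. The 3-month contrast has a larger standard error than the pooled effect, about 0.105 against 0.077 SD under the assumptions above, but it is the quantity for which the sample size was computed.

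### The primary mixed model has no term for PM+ group or household, so with any positive intraclass correlation its standard error is too small and its test exceeds 5%

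*Protocol article*

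**What the plan says.** Under Statistical methods, the article sets out the linear mixed model for the primary endpoint: intervention as a fixed effect, with "baseline measurement of primary endpoint as covariate, and participants as random effects". Participant is the only random effect named. Hierarchical and multilevel modelling are mentioned in the same section, but no group, facilitator or household level is attached to either term. The multilevel wording serves only to justify not imputing missing values.

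Under Group PM+, sessions are separated by gender and "gender-matched facilitators will lead groups consisting of six to eight participants (T1". Enhanced care as usual (E-CAU) is a leaflet on available services, with no grouping.

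Under Randomization, "participants will be randomly assigned on a 1:1 basis", but "participants from the same household will be assigned to the same intervention arm". The reason given is to limit contamination, and shared households are described only as something that may occur.

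Under Sample size and power calculations, the target is a "conservatively estimated small to medium Cohen’s d effect size of 0.4 in the PM+ group at the 3-month follow-up", with "power = 0.90, a = 0.05, two-sided". No ICC or design effect is mentioned.

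**The concern.** A participant random effect accounts for the correlation between visits of one person. It says nothing about correlation between people, and the design produces that in two ways.

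- **Treatment groups.** PM+ participants share a group and its facilitator over five weekly sessions. The Background itself lists benefit from fellow group members as an advantage of the format. E-CAU participants are not grouped, so the design is partially nested.
- **Households.** Where several members of a household enrol, they are allocated together. For them the household is in effect the unit of randomisation, in both arms.

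If outcomes are positively correlated within either unit, the arm difference varies more than the stated model allows. The primary confidence interval is then too narrow and the test rejects too often. The Discussion links a positive result to dissemination and scale-up, so the error rate of this test matters.

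**Working it through.** **1. The plan's own figure.** Inputs from the sample size section: d = 0.4, two-sided alpha 0.05, power 0.90, 30% attrition.

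- Normal approximation: n = 2 × (1.960 + 1.282)² / 0.4² = 131.3, so 132 per arm.
- Noncentral t: 132 per arm gives power 0.899 and 133 gives 0.901, so 133. The article says "Power calculations suggest a minimum sample size of 133 participants per group".
- Attrition: 133 / 0.70 = 190 per arm, 380 in total. The article says "Considering an expected 30% attrition at the 3-month follow-up, we aim to include a total number of 380 participants".

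The figures reproduce exactly for independent observations. The sample size therefore contains no allowance for clustering either.

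**2. Number of groups.** 190 / 8 = 23.8 and 190 / 6 = 31.7, so about 24 to 32 PM+ groups if everyone in that arm is placed.

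**3. Effect of group clustering.** Assumptions: groups of 7, 30% attrition spread evenly, so m = 7 × 0.70 = 4.9 retained; equal total variance in the two arms; ICC over a range, as none is given.

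- Design effect in the PM+ arm: DE = 1 + (m − 1) × ICC. In the E-CAU arm it is 1.
- True variance of the difference relative to the modelled variance: F = (DE + 1) / 2.
- Shortfall in the standard error: 1 − 1/√F.
- Actual type I error: 2 × [1 − Φ(1.96/√F)].

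| Group ICC | DE | F | SE too small by | Type I error |
|---|---|---|---|---|
| 0.01 | 1.039 | 1.020 | 1.0% | 5.22% |
| 0.02 | 1.078 | 1.039 | 1.9% | 5.45% |
| 0.05 | 1.195 | 1.098 | 4.5% | 6.14% |
| 0.10 | 1.390 | 1.195 | 8.5% | 7.30% |

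Simulations of an analysis that ignores groups, under these conditions, gave 5.3% at ICC 0.01, 6.1% to 6.7% at 0.05 and 7.4% to 7.6% at 0.10, in line with the formula.

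**4. Sensitivity.** If attrition did not thin the groups (m = 7), the type I error would be 6.8% at ICC 0.05 and 8.6% at 0.10. Simulation (10,000 runs each) gave the same values, and using the between-group variance in the PM+ arm brought them back to 5.1% and 5.2%. In the other direction, if 30% of the PM+ arm carried no group effect because they never attended (an assumption), simulation gave about 5.5% at ICC 0.05 and 6.0% at 0.10.

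**5. Households.** Here DE = 1 + (h − 1) × ICC applies in both arms, with h the mean number of participants per household. The article gives neither quantity. Taken alone, h = 1.2 with ICC 0.1 gives DE 1.02 and a type I error of 5.2%; h = 2 with ICC 0.3 gives DE 1.30 and 8.6%. A span that wide shows only that the contribution cannot be fixed from the article.

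**The case against.** **A journal article leaves detail to the analysis plan.** That would answer silence. Here the fixed effect, the covariate and the random effect of the primary model are all stated, and the stated structure omits levels that the design creates. The hierarchical and multilevel wording does not repair this, because the only level named is the participant.

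**The inflation is conditional and may be small.** This stands. With an ICC near zero nothing is lost, and at 0.01 the effect is negligible. Intention-to-treat analysis also keeps participants who never joined a group, which dilutes the correlation. The modest size lowers the priority of the point but does not make the model right.

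**Shared households may be rare.** This also stands, and is why no single household figure is given. Group clustering does not depend on it.

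Three stronger readings are tempting and not supported:

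- *All secondary outcomes are affected in the same way.* The participant-only structure is stated for the primary endpoint. No random-effects structure is given for the secondary outcomes.
- *The economic bootstrap is wrong.* The Economic analyses section gives 10,000 resamples but no resampling unit. That is a detail left out, not an error made.
- *The trial is underpowered.* The sample size has no design effect, but without an ICC a shortfall cannot be established. The calculation also takes no credit for the baseline covariate that the model includes.

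**Conclusion.** The point holds for the primary analysis. As written, the model treats participants as independent, while the design puts one arm into treatment groups and allocates households as units. For any positive ICC the primary standard error is too small and the test is anti-conservative.

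For group clustering the size is modest: a type I error of roughly 5.2% to 7.3% for ICCs of 0.01 to 0.10, under the assumptions of groups of 7, 4.9 retained and equal variances. It is lower with much non-attendance and higher if groups stay full. Household clustering would add to this by an unknown amount. A reader might infer that the nominal 5% level certainly fails, but the article gives no ICC, so the statement has to remain conditional. This should be fixed, since the correction is cheap and bears on the confirmatory test. It does not call the trial's design into question.

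**What to change.** In the primary model:

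- Add a random effect for PM+ group in the PM+ arm only. Code E-CAU participants, and PM+ participants never placed in a group, as singletons.
- Account for household with a random effect or household-robust standard errors. Treat household and group as crossed: groups are separated by gender, so a man and a woman from one household sit in different groups.
- Use small-sample degrees of freedom, because there are only about 24 to 32 groups. Confirm that the named Stata version supports them, or name software that does.
- Record group and household identifiers in the analysis data, and state the change before unblinded analysis.

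The cost is analysis wording and two identifiers that the trial must already hold in order to allocate and deliver PM+. Intervals become slightly wider. On the plan's own basis (133 evaluable per arm, d = 0.4), power with the correct variance is Φ(0.4/√(2F/133) − 1.96): about 88% at a group ICC of 0.05 and 85% at 0.10, against the planned 90%, before any gain from the baseline covariate.
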